**Methods:**

10 primary care practices will be recruited to the study (5 intervention, 5 control). Within each practice, individuals at high risk of impaired glucose regulation will be identified using an automated version of the Leicester Risk Assessment tool. Individuals scoring within the 90^th^ percentile in each practice will be invited to take part in the study. Practices will be assigned to either the control group (advice leaflet) or the intervention group, in which participants will be invited to attend a 3 hour structured educational programme designed to promote physical activity and a healthy lifestyle. Participants in the intervention practices will also be invited to attend annual group-based maintenance workshops and will receive telephone contact halfway between annual sessions. The study will run from 2010–2014.

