## Methods

### Study design

This study is a clustered randomised controlled trial. Randomization will be conducted at the level of the GP practice by a trained individual who is independent of the study team. Practices were randomised (1:1) to receive control conditions or a structured education programme. A blocked design stratified for practice size was used. The study is designed to adhere to internationally recognized criteria for developing complex interventions [15] and for undertaking and reporting cluster randomised controlled trials [16]. Follow-up will be conducted at 12, 24 and 36 months in order to establish the longer-term effectiveness of the programme and determine the natural history of progression to type 2 diabetes over three years in a high risk UK cohort identified through a risk score in primary care. See Figure 1 for a flow-diagram of the study design. 

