### Sample size

This study was powered to detect a difference in change in ambulatory activity of 2000 steps per day between groups; a difference of this magnitude reflects the primary behaviour change aim of the intervention programme and is consistent with the national physical activity recommendations and the intervention effect observed in the proof of concept study that preceded this trial [9,17]. Previous studies with a follow-up of between 3 to 12 months have reported a standard deviation of change in ambulatory activity of 2500–4000 steps per day in relevant populations [9,18-20]. Therefore, in order to detect a difference of 2000 steps per day between groups, assuming a standard deviation of 4000 steps per day, a power of 90%, a significance of 0.05, a cluster size of 90 (see section titled Participants below) and an intracluster correlation coefficient of 0.02 [21], we require a minimum of 8 clusters. In order to account for potential dropout at the practice level and comply with guidance from the Medical Research Council for minimum cluster numbers [22], 10 GP practice clusters will be recruited to this trial.

This sample size will also have sufficient power to enable clinically significant differences to be detected between groups for change in important secondary outcomes. For example, based on a power of 80%, a significance of 0.05 and a intracluster correlation coefficient of 0.02 [23], the above sample size will allow for a reduction in 2-h glucose of 0.8 mmol/l (based on a standard deviation of 2 mmol/l standard deviation [24]) and a reduction in HbA1c of 0.2% (based on a standard deviation a standard deviation of 0.5% [24,25]) to be detected.

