### Participants

Ten GP practices will be recruited from the Leicestershire region (city and county primary care trusts). Initial contact with each GP practice will be through a letter of invitation to take part. All recruited practices will have an induction visit from the study co-ordinator who will provided training and support for the administrative staff in each of the study sites. Eligible participants will be identified using an automated version of Leicester Risk Assessment tool developed and validated by our group [26]. The automated risk score uses the Morbidity, Information Query and Export Syntax (MIQUEST) programme, designed to extract data from computerized medical records in primary care, to analyse data from six variables (age, sex, ethnicity, BMI, family history of type 2 diabetes, antihypertensive medication status) that are commonly held on local PCT databases. By assigning pre-validated weighting to each variable, individuals are ranked by their risk of undiagnosed impaired glucose regulation or type 2 diabetes with a higher score indicating higher risk. The risk score is calculated as follows:

Risk factor Score = 0.0407 x age

+  0.296 (if male, no change in female)

+ 0.934 (ethnicity, as a practice proportion of south Asians)

+ 0.0859 x BMI

+ 0.440 (if family history of type 2 diabetes, no change otherwise)

+ 0.374 (if on antihypertensive medication, no change otherwise)

In this study, high risk individuals will be classified as those above the 90^th^ percentile of the calculated risk score. Eligible individuals will be sent a letter of invitation, a patient information sheet and stamped addressed envelope by a member of their GP practice. Contacted individuals will be requested to return a reply slip confirming or declining their interest in taking part; those who wish to take part will be contacted by the study team where a baseline consent appointment is arranged. 

Individuals will be excluded from the study if they have an existing diagnosis of type 2 diabetes or are diagnosed with type 2 diabetes at baseline, are taking steroids or are unable to speak English; our experience suggests this approach does not limit recruitment and is able to produce a study population that fully reflects the ethnic makeup of the local population.

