#### Anthropometric and demographic variables

Arterial blood pressure will be measured in the sitting position (Omron, Healthcare, Henfield, UK); three measurements will be obtained and the average of the last two measurements will be used. Body weight and body fat percentage (Tanita TBE 611, Tanita, West Drayton, UK), waist circumference (midpoint between the lower costal margin and iliac crest) and height will also be measured, to the nearest 0.1 kg, 0.5% and 0.5 cm respectively. Information on current smoking status, medication history, and ethnicity is obtained by self-report. Social deprivation will be determined by assigning an Index of Multiple Deprivation (IMD) score to participant postcodes [39]. IMD scores are publicly available continuous measures of compound social and material deprivation which are calculated using a variety of data including current income, employment, health, education, and housing.

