### Data analysis

The study will be reported according to the internationally recognised CONSORT statement for the reporting of cluster randomised control trials [16]. Those withdrawn from the study due to a diagnosis of type 2 diabetes will have their last observation carried forward. Sensitivity analysis, using multiple imputation, will be used to assess the effect of those missing to follow-up. Random effects regression models, controlled for baseline value and taking into account cluster, will be used to look at the difference between groups in change from baseline in continuous outcome measures after checking for normality and applying transformation techniques where necessary. Extreme outliers (more than 4 standard deviations from the mean) will be removed from the analysis. Survival curves will be calculated to estimate the cumulative incidence of diabetes. The difference in incidence of diabetes in the groups will be tested using the two-sided log-rank test. Statistical significance will be assessed at the 5% level and all analysis will be 2-sided.

Interim analysis will be conducted and reported at 12 months.

In concordance with other physical activity randomised controlled trials undertaken by our group and others [46,47], we will undertake pooled analysis of the study cohort to determine, through regression analysis techniques, the extent to which change in physical activity is associated with change in key biochemical and anthropometric variables; this will help provide additional information quantifying the strength of the association between physical activity and metabolic health in a population with a high risk of type 2 diabetes; any such analysis will be reported with the caveats inherent in undertaking additional pooled cohort analysis within the context of a randomised controlled trial.

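### With 5 v 5 practices stratified only on size, the stated continuous-outcome model is valid but leaves unused the age, sex, ethnicity and deprivation data already collected; pre-specifying them is an optional gain in precision.

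*Protocol article*

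**What the plan says.** The Data analysis section of the protocol article gives one model for all continuous outcomes: "Random effects regression models, controlled for baseline value and taking into account cluster, will be used to look at the difference between groups". The quantity compared is change from baseline. The article names no covariate other than the outcome's own baseline value, and the only other term is cluster.

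The design around that model is as follows.

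- **Clusters.** The abstract gives ten practices, five per arm. The Participants section draws them from both city and county primary care trusts.
- **Restriction of the randomisation.** The Study design section says: "A blocked design stratified for practice size was used". No other balancing factor is mentioned.
- **Sample size inputs.** The Sample size section works with "assuming a standard deviation of 4000 steps per day, a power of 90%, a significance of 0.05, a cluster size of 90", an intracluster correlation of 0.02 and a target difference of 2000 steps/day.
- **Available variables.** Age and sex are inputs to the automated risk score (Participants). Ethnicity is recorded by self-report, and "Social deprivation will be determined by assigning an Index of Multiple Deprivation (IMD) score to participant postcodes" (Anthropometric and demographic variables).

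**The concern.** With five practices per arm, chance alone can give the arms a different mix of patients. Three features of the design make such differences between practices likely. Practices come from both city and county areas. The abstract sets eligibility by a percentile within each practice, not by a common cut-off. The risk score itself carries a practice-level South Asian proportion, so the authors recognise that ethnic mix varies by practice.

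Stratification on practice size does not directly balance ethnicity, age or deprivation. If these variables predict change in the outcome beyond its baseline value, the model as stated leaves that part of the between-practice variation in the estimate and its standard error. Recruiting more patients per practice reduces only the within-practice part. Adjustment for individual covariates can reduce the between-practice part with little use of the scarce practice-level degrees of freedom.

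What is at stake is precision, and how readily a reader can attribute a result to which practices fell in which arm.

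**Working it through.** **Inputs.** All are from the Sample size section, except the five practices per arm, which come from the abstract: SD 4000, ICC 0.02, cluster size m = 90, k = 5 practices per arm, target 2000 steps/day, two-sided 5%, power 90%.

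**1. The plan's own figure.** Without clustering, 85 participants per arm are needed. The design effect is 1 + 89 × 0.02 = 2.78. This gives 85 × 2.78 = 236.3 per arm, and 236.3 / 90 = 2.63 clusters. Adding one cluster per arm for the small number of clusters gives 3.63, rounded up to 4 per arm, or 8 in all. A cluster-level t-test agrees: power is 74% with 3 per arm and 91% with 4. The stated minimum of 8 is reproduced. With the planned 5 per arm, power is 97.5%.

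**2. Where the variance lies.**

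Var(arm difference) = (2/k) × SD² × [ICC + (1 − ICC)/m] = 0.4 × 4000² × (0.02 + 0.98/90) = 0.4 × 16,000,000 × 0.03089 = 197,689.

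- SE = √197,689 = 444.6 steps/day.
- Between-practice share = 0.02 / 0.03089 = 65%.
- Between-practice SD = 4000 × √0.02 = 566. Its contribution to the arm difference has SD 566 × √(2/5) = 358 steps/day, which is 18% of the 2000-step target.

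These figures use the sample-size SD and ICC, so they precede any reduction from baseline adjustment.

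**3. Possible gain from covariates.** Let the four covariates remove a fraction r of the between-practice term beyond what baseline removes. The documents give no value for r, so the range is an assumption.

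| r | Bracketed term | SE | Reduction | Equivalent number of practices |
|---|---|---|---|---|
| 0 | 0.03089 | 445 | 0% | 10 |
| 10% | 0.02889 | 430 | 3% | 10.7 |
| 25% | 0.02589 | 407 | 8% | 11.9 |
| 50% | 0.02089 | 366 | 18% | 14.8 |

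The last column is 10 × 0.03089 / (bracketed term). If the covariates also explained up to 10% of within-practice variance, the SE would be 437–445 at r = 0, 398–407 at r = 25% and 356–366 at r = 50%.

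**4. Size of chance imbalance.** For any practice-level characteristic, the SD of the 5 v 5 arm difference is √(2/5) = 0.63 between-practice SDs. The chance of a difference larger than one such SD is about 11%. If the South Asian share had a between-practice SD of 0.25 to 0.30 (an assumption), the SD of the chance arm difference would be 0.63 × 0.25 to 0.63 × 0.30, about 16 to 19 percentage points.

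**5. Validity of the stated approach.** A cluster-level t-test was simulated with 5 v 5 practices, 40,000 trials per setting. An unadjusted practice characteristic explained none, half or all of the between-practice variance. Type I error was 4.9–5.0% in each case and the mean arm difference was close to zero.

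**The case against.** The strongest reply is that nothing here is wrong. Baseline-adjusted random-effects regression is an accepted primary analysis for a cluster trial, and the article does not exclude further covariates. A full covariate list is often left to a statistical analysis plan, which is not at hand. This stands in part: the planned model is valid. But the sentence does name an adjustment set for all continuous outcomes and does not defer the choice. Adding to that set in advance is therefore a specific change to a stated method.

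A reader might infer that case-mix differences bias the arm comparison. The documents do not support that. Allocation is random, so what remains is chance variation, and an analysis that handles cluster properly carries it in the standard error, as step 5 shows. A reader might also infer that the trial is underpowered without the covariates. It is not. Power for 2000 steps is 97.5% with five practices per arm, and the assumed gains would lift it only to about 98–99.7%. For 2-h glucose and HbA1c, power is about 88% against the 80% stated.

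Three further points stand:

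- Adjusting for the outcome's own baseline already removes case mix that acts through baseline. Only what predicts change given baseline is left, and the documents do not show how large that is. It could be near zero.
- Individual covariates remove practice-level imbalance fully only if within-practice and between-practice effects agree.
- Practice size, the stratification factor, is also absent from the stated model and would be a natural candidate for adjustment.

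**Conclusion.** The point holds as an optional precision improvement. The stated model is valid and unbiased. It simply does not use four prognostic candidates that the trial will hold anyway, in a design with few clusters and one stratification factor. On the plan's inputs about 65% of the variance of the arm difference lies between practices, with an SE of about 445 steps/day before baseline adjustment.

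The possible reduction in SE, 0 to 18%, rests entirely on the assumption that the covariates explain 0 to 50% of the between-practice component beyond baseline. The 16 to 19 point figure for ethnic imbalance rests likewise on an assumed spread between practices. Type I error, the eight-cluster minimum and the stated power are unaffected, and no trial objective fails if the change is not made.

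**What to change.** In the Data analysis section, and in the statistical analysis plan if there is one, state that the primary and all other continuous-outcome models adjust for the outcome's baseline value plus individual age, sex, ethnicity and IMD score as pre-specified fixed effects, with practice as a random effect. Keep the model with baseline value and cluster alone as a supporting analysis. The set should be fixed before outcome data are seen, so that it is not chosen in response to an observed imbalance between the arms.

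The cost is one sentence, with no new data collection. A few missing ethnicity entries or postcodes would need simple baseline imputation. The gain may turn out to be small.

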### Secondary outcomes

#### Biochemical variables

This study will measure relevant markers of metabolic and renal health including fasting and 2-h post challenge glucose, HbA1c, lipid profile, liver function tests (albumin, total bilirubin, alkaline phosphatase [ALP], alanine transaminase [ALT]), urea and electrolytes (sodium, potassium, creatinine). Analysis is conducted in the same laboratory located within Leicester Royal Infirmary, UK, using stable methodology standardized to external quality assurance reference values.

Participants will be invited to attend each clinical measurement session after a 12-h fast and 24 h of avoiding vigorous intensity exercise. In concordance with WHO recommendations, those who have a fasting or 2-h blood glucose level in the diabetes range at any clinical measurement session will be called back for a confirmatory oral glucose tolerance test [38].

All venepuncture and OGTT timings will be undertaken by trained phlebotomists who are not part of the scientific advisory team for this study and who are blinded to treatment allocation. All biochemical analysis will also be conducted blinded to treatment group.

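### The 4 SD outlier rule can delete genuine extreme values from continuous secondary outcomes such as HbA1c, with no error check and no analysis that keeps them

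*Protocol article*

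**What the plan says.** The rule stands in Methods, Data analysis: "Extreme outliers (more than 4 standard deviations from the mean) will be removed from the analysis". It carries no condition. It follows directly on the sentence about random effects models, which concern "change from baseline in continuous outcome measures after checking for normality and applying transformation techniques where necessary".

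Three other statements bear on it:

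- People who leave because of diabetes stay in the continuous analyses: "Those withdrawn from the study due to a diagnosis of type 2 diabetes will have their last observation carried forward".
- The only sensitivity analysis named concerns absent data: "Sensitivity analysis, using multiple imputation, will be used to assess the effect of those missing to follow-up". A value that was observed and then deleted is not of that kind.
- Diabetes incidence is analysed separately: "The difference in incidence of diabetes in the groups will be tested using the two-sided log-rank test".

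Under Biochemical variables, the article provides for a second glucose tolerance test to confirm a high result: "those who have a fasting or 2-h blood glucose level in the diabetes range at any clinical measurement session will be called back". The Sample size section gives 2-h glucose and HbA1c their own power statements, for example "a reduction in 2-h glucose of 0.8 mmol/l (based on a standard deviation of 2 mmol/l".

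**The concern.** A value is dropped because of what the outcome turned out to be after randomisation, not because it is known to be wrong. The population is selected for high diabetes risk, so a few very high glucose or HbA1c values are to be expected as real results. A participant whose diabetes has been confirmed by a second test could still have the glucose value behind that diagnosis struck out for being large. If the value is carried forward to later visits, it could be struck out there too.

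If the intervention works, such values should be more frequent in the control arm. Deleting them then takes out more control-arm failures than intervention-arm failures and pulls the difference toward zero. It also understates the outcome's variance. No planned analysis would show the reader how much depended on the deletion.

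**Working it through.** The article gives no figure for the effect of the rule, so there is none to reproduce.

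**Inputs from the article (Sample size, Participants).** 10 practices of 90 = 900 people, 450 per arm at 1:1. SDs: 4000 steps/day, 2 mmol/l for 2-h glucose, 0.5 percentage points for HbA1c. Intracluster correlation 0.02.

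**Where the cut falls at the planned SDs.**
- Steps: 4 × 4000 = 16,000 steps/day from the mean
- 2-h glucose: 4 × 2 = 8 mmol/l
- HbA1c: 4 × 0.5 = 2.0 percentage points

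**Normal data.** P(|Z| > 4) = 2 × (1 − Φ(4)) = 0.0000633; × 900 = 0.057 values. The rule is idle, for the primary outcome as for any other.

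**Skewed data left untransformed (assumed lognormal).** With log-SD s, mean = exp(s²/2), SD = mean × √(exp(s²) − 1), and the cut is mean + 4 SD.
- s = 0.75: tail 0.88%, 7.9 of 900 deleted, mean falls 4.4%
- s = 1.0: tail 0.99%, 8.9 of 900 deleted, mean falls 8.2%

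After a log transformation the same data are normal and the count returns to 0.057.

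**2-h glucose as a mixture (assumed).** 10% of controls and 6% of the intervention arm progress; progressors N(13, 2.5), others N(6, 1.6), in mmol/l; cut from the pooled mean and SD.
- Pooled mean = 6 + 0.08 × 7 = 6.56
- Variance = 0.92 × 1.6² + 0.08 × 2.5² + 0.08 × 0.92 × 7² = 6.46; SD = 2.54
- Upper cut = 6.56 + 4 × 2.54 = 16.7
- P(progressor above cut) = P(Z > (16.73 − 13)/2.5) = P(Z > 1.49) = 0.068
- Deleted: control 45 × 0.068 = 3.1; intervention 27 × 0.068 = 1.8
- Arm means before: 6.70 and 6.42, difference 0.280. After: 6.624 and 6.373, difference 0.251. The loss is about 0.03 mmol/l, or 11%.

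With the cut made on log values, it lies near 25 mmol/l. Simulation (4,000 replicates, values floored at 2.5) then deletes essentially nobody and leaves the difference unchanged.

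**Heavier tails (assumed).** In this simulation, control progression is halved by the intervention, and progressors' excess above an assumed cut-off (11.1 mmol/l or 6.5%) is exponential. Control progression is 6–15% for 2-h glucose and 6–10% for HbA1c.

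| Outcome | Scale of cut | Values deleted of 900 | Shrinkage |
|---|---|---|---|
| 2-h glucose | raw | 3.6–10.2 | 4–22% |
| 2-h glucose | log | 0.04–2.3 | 0.1–7% |
| HbA1c | raw | 4.9–13.1 | 8–33% |
| HbA1c | log | 3.1–12.9 | 6–34% |

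The largest HbA1c losses (29–34%) come from scenarios whose SD is 0.79–0.98, well above the planned 0.5. Where the simulated SD is 0.45–0.50, the loss is 6–10%. With 10% progression in both arms (2-h glucose, raw scale), about 3.5 values go from each arm and there is no bias.

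**The case against.** The best defence is the order of the sentences. Normality is checked and a transformation applied where needed before the rule is reached, so ordinary skew may be gone by then. For lognormal data and for the 2-h glucose mixture above, that removes the problem entirely. This stands, and it confines the concern to outcomes that remain heavy-tailed. HbA1c is the clearest candidate, because under the assumed tails the log scale barely helps.

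The bias is also small against sampling error. With design effect 1 + 89 × 0.02 = 2.78, the standard error of the 2-h glucose difference is 2.54 × √(2 × 2.78/450) = 0.28 mmol/l, or 0.22 at the planned SD of 2. A shift of 0.03 is roughly a tenth of that, and the design targets 0.8. Where the intervention has the expected direction the shift is conservative. This stands too.

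It may be said that error checks and sensitivity sets belong in an analysis plan that is not shown. That is fair for details such as whether the mean and SD are pooled or by arm. It does not cover the rule itself, which the article states outright and without condition.

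Three stronger readings are tempting, and the article does not support them:
- **The rule threatens the primary result.** At the planned SD a value must lie 16,000 steps/day from the mean, eight times the 2000-step target, so the rule is nearly inert unless step changes are heavily skewed.
- **People who progress are lost from the diabetes comparison.** That comparison is a log-rank test on time to diagnosis, which a rule on continuous values does not touch.
- **Carrying values forward contradicts the outlier rule.** The two can be applied in sequence, and the article does not say that the carried value is in the diabetes range. It is only possible that a carried value is later deleted.

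**Conclusion.** The point holds in a limited form. The article fixes a deletion rule based on size alone, with no error check and no analysis that retains the values. Where the data are near normal, the rule has no purpose. Where it acts, it can remove real outcomes from continuous secondary measures, and if extremes are more common in one arm it can pull the estimated difference toward zero.

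The size cannot be fixed from the article, which gives no progression rates or tail shapes. On the assumptions shown it runs from nothing (equal arms, or 2-h glucose cut on the log scale), through about 11% or 0.03 mmol/l (2-h glucose, raw scale), to about a third in the heaviest HbA1c tails tried. These calculations use outcome levels, not baseline-adjusted change, so they are illustrations, not forecasts. Bias is possible, not certain. Severity is moderate: worth correcting before analysis, but no threat to the primary outcome or the incidence test.

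**What to change.** Replace the sentence. Keep every valid value in the main analysis. Exclude a value only if a measurement, device, laboratory or data-entry error has been verified by someone blind to arm. If the 4 SD exclusion is still wanted, report it as a sensitivity analysis beside the main result.

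The cost is one sentence in the plan and slightly wider confidence intervals for skewed outcomes. The sample size does not change.

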Based on a typical GP practice of 4500 adults without known type 2 diabetes, 450 will be eligible for inclusion into the study based on the risk score. Of these we anticipated that 330 (75%) will meet the initial inclusion criteria and be invited to take part in the study. Around 100 (30%) are then expected to consent to take part, of which 10 (10%) will have screen detected type 2 diabetes and therefore excluded at baseline; therefore we anticipate the average cluster size to be 90 individuals (see sample size calculation).

Those diagnosed with diabetes over the course of the study will be informed of their diagnosis and referred back to their health care team for standard care. Progression to type 2 diabetes will be included as a secondary outcome.

Figure 1 shows the flow of the participants through the study.

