Professional story	Use simple non-technical language, analogies, visual aids and open questions to provide participants with:	·Individuals are helped to plot their individual risk (fasting and 2 hour blood glucose levels, cholesterol and blood pressure levels - assessed at baseline)	·Common Sense Model [27]	35 minutes
			·Dual Process Theory [32]	
	·An overview of healthy glucose metabolism			
			·Social Cognitive Theory [30]	
	·The aetiology of diabetes			
	·An overview of the macrovascular complications associated with being ‘at risk’ of type 2 diabetes.			
Risk story	·The meaning and assessment of risk in the context of developing type 2 diabetes	·Participants are supported to plot their own risk factors onto a risk chart to work out their individual risk areas.	·Dual Process Theory [32]	25 minutes
			·Social Cognitive Theory [30]	
	·Explore personal risk of developing type 2 diabetes			
Break	Refreshments and informal discussion			10 minutes
Physical activity	Use simple non-technical language, analogies, visual aids and open questions to help participants:	·Individuals are helped to plot their individual steps per day scores (assessed at baseline)	·Social Cognitive Theory [30]	55 minutes
			·Implementation Intentions [31]	
	·Identify how physical activity improves glucose control;			
	·Understand the current physical activity recommendations	·Participants are provided with a physical activity diary and encouraged to set their first action plan.		
	·Explore options for incorporating physical activity (primarily walking) into everyday life			
	·Identify barriers to exercise			
	·Form action plans			
	·Use their provided physical activity diaries			
	·Set personal goals (based on baseline pedometer counts)			
			·Dual Process Theory [32]	
Diet	·Give participants an accurate understanding of the link between dietary macro-nutrients and metabolic dysfunction	·Participants are asked to group models of fats and oils into saturated, polyunsaturated and monounsaturated categories.	·Social Cognitive Theory [30]	20 minutes
			·Dual Process Theory [32]	
Conclusion	Questions and future care	Sign-post to locally available groups/programmes		5 minutes

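### Progression to type 2 diabetes, a secondary outcome, is tested by a log-rank test with no baseline glucose covariate, which gives up a modest and uncertain amount of precision that could be recovered at almost no cost

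*Protocol article*

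**What the plan says.** In the protocol article, the Participants section gives progression to diabetes its status: "Progression to type 2 diabetes will be included as a secondary outcome". The Data analysis section gives its between-arm test: "The difference in incidence of diabetes in the groups will be tested using the two-sided log-rank test". It names no covariate and no cluster term for that test. For continuous outcomes the same section says: "Random effects regression models, controlled for baseline value and taking into account cluster, will be used". All tests are two-sided at the 5% level.

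Under Biochemical variables, the outcomes include "fasting and 2-h post challenge glucose, HbA1c, lipid profile". A fasting or 2-h value in the diabetes range at any measurement session leads to a confirmatory glucose tolerance test. Table 1, in the Intervention section, has participants plot their "fasting and 2 hour blood glucose levels, cholesterol and blood pressure levels - assessed at baseline". That table describes the intervention arm, but people found to have diabetes at baseline are excluded and continuous outcomes are analysed as change from baseline. The baseline glucose values must therefore exist in both arms.

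Ten practices are randomised 1:1, stratified for practice size only (Study design; Sample size).

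**The concern.** The event is defined by glucose reaching a threshold, so baseline glucose is the starting value of the variable that defines it. Entry is by risk score rather than by glucose, and only those already in the diabetes range are removed. Participants can therefore start anywhere from normal glucose to just below the threshold. A prognostic variable of this kind is already on file, and the plan uses baseline values for continuous outcomes but not here.

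At stake is precision. With 5 practices against 5, variation in baseline glycaemia within and between practices adds noise to the diabetes comparison, and part of that noise could be removed.

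**Working it through.** **Plan's own figure.** The article states no power or event count for diabetes. Its cluster count for steps can be reproduced, which confirms the design effect used below:
- Per arm without clustering: 2 × [(4000/2000) × (1.960 + 1.282)]² = 84.1.
- Design effect: 1 + (90 − 1) × 0.02 = 2.78.
- Clusters per arm: 84.1 × 2.78/90 = 2.60. Adding one per arm for the small number of clusters gives 3.60, rounded up to 4, or 8 in all, as stated.

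**Chance imbalance in baseline 2-h glucose.** The Sample size section gives an SD of 2 mmol/l and an ICC of 0.02 when it considers change in 2-h glucose. Applying them to baseline glucose is an assumption.
- SE of the arm difference in SD units: √(2 × 2.78/450) = 0.111. In mmol/l: 2 × 0.111 = 0.22.
- Resulting 95% range for the diabetes hazard ratio: exp(±1.96 × 0.111 × ln h), where h is the assumed hazard ratio per SD of glucose. This gives 0.90-1.12 for h = 1.65, 0.86-1.16 for h = 2.0 and 0.81-1.24 for h = 2.7.

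A valid practice-level test already carries this spread in its standard error. It describes the noise and should not be added to the power loss below.

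**Power at practice level, no residual practice effect.** The simulation had 10 practices of 90, one baseline covariate with ICC 0.02, complementary log-log events and 1,500 trials per setting. It compared a t test on practice proportions with a t test on practice-mean residuals from a logistic regression on baseline glucose. Incidence, hazard ratio and h are assumptions.

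| Incidence, hazard ratio | h = 1.65 | h = 2.0 | h = 2.7 |
|---|---|---|---|
| 10%, 0.5 | 67 to 70% | 62 to 67% | 58 to 67% |
| 10%, 0.6 | 44 to 46% | 41 to 47% | 39 to 45% |
| 15%, 0.5 | 81 to 85% | 80 to 86% | 74 to 85% |
| 15%, 0.6 | 59 to 63% | 57 to 62% | 52 to 63% |

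Repeat runs gave gains from about 1 point to 12 points (the largest 51 to 63%, at 15% incidence, hazard ratio 0.6, h = 2.7). Type I error was 4-6% for both t tests. Simulation error on one power figure is up to √(0.5 × 0.5/1500) = 1.3 points.

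**The same with residual practice variation, SD 0.3 on the log-hazard, hazard ratio 0.6.**

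| Incidence | h = 1.65 | h = 2.0 | h = 2.7 |
|---|---|---|---|
| 10% | 30.9 to 31.7% | 27.9 to 30.1% | 26.0 to 30.8% |
| 15% | 36.7 to 37.4% | 34.8 to 36.9% | 32.0 to 36.0% |

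The gains are 0.7 to 4.8 points, and about 0-3 points if 20% are also lost to follow-up. At a smaller residual SD of 0.2 (15% incidence, hazard ratio 0.5), the gain was 3 points at h = 1.65 and 10 at h = 2.7.

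**The named test itself.** A further simulation compared the log-rank test with a Cox model adjusted for one baseline covariate (hazard ratio 0.6, 20% loss, no residual practice effect, 1,000 runs per setting).
- At 6% incidence there was no real gain (about 32-35% against 32-34%).
- At 12%, power went from 58 to 59% with a log-hazard ratio of 0.5 per SD, and from 56-57 to 61-62% with 1.0.
- At 18%, power went from 76 to 76-79% with 0.5, and from 68-73 to 79% with 1.0.

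With a residual practice SD of 0.3 and no true effect, the log-rank test rejected in 11-21% of runs and the adjusted Cox model in 10-21%. Adding the covariate does almost nothing about clustering.

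**The case against.** The strongest reply is that nothing here is an error. The log-rank test is standard for incidence, and omitting a prognostic covariate does not invalidate it. Progression is one of several secondary outcomes, and the article makes no power claim for it. The glycaemic outcomes for which power is claimed, 2-h glucose and HbA1c, already have baseline-adjusted, cluster-aware models. A supporting adjusted model may sit in an analysis plan that is not shown. All of this stands, and it limits the point to one of efficiency. It does not remove the point, because the article itself names the between-arm test and that test excludes the covariate.

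A reader might infer that an unadjusted test leaves the diabetes result biased by chance imbalance between 5 and 5 practices, as a harm beyond lost power. The documents do not support this. Randomisation makes such imbalance part of sampling error, and practice-level type I error stayed at 4-6% without adjustment.

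A reader might also expect a gain of 5 points or more. That needs an association of about 2 per SD or stronger and little other variation between practices. The article supports neither.

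The last objection concerns the remedy. A random-effects model judged by an ordinary Wald z test is not safe with 10 practices. In a single-period complementary log-log version (400 runs), null rejection was 7.5% at residual practice SD 0.3 and 9.8% at 0.5. This stands, and the fix below includes a correction for it.

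**Conclusion.** The point holds as an avoidable, modest loss of precision on a secondary outcome. Under the assumed incidence of 10-15%, hazard ratio of 0.5-0.6 and association of 1.65-2.7 per SD, adjustment is worth about 1-12 points of power if baseline glucose is the only thing that differs between practices, and about 0-5 points at a residual practice SD of 0.3. At lower incidence the gain may vanish. None of these inputs is in the article, and neither are the SD and ICC of baseline glucose.

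It would go too far to call the log-rank test invalid for want of a covariate, or to call progression the trial's key clinical outcome, a label the article does not use. The absence of any cluster term in the same sentence is a separate and potentially larger matter that baseline adjustment leaves nearly unchanged. It makes sense to deal with both in one revision.

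**What to change.** In the Data analysis section, replace the log-rank test as the between-arm test of diabetes progression with a cluster-aware analysis that includes baseline 2-h glucose and fasting glucose as pre-specified continuous covariates and a small-cluster correction for 10 practices. Either of these would serve:
- a t test on practice-level residuals from a model of progression on baseline glucose, with 10 − 2 = 8 degrees of freedom; or
- a grouped-time complementary log-log model by annual visit, with a practice random effect and few-cluster degrees of freedom in place of the normal approximation.

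Keep the survival curves and the unadjusted comparison as description.

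The cost is a sentence or two and one model, with no new measurements or visits. There are two small downsides: a model-based hazard ratio is conditional on baseline glucose, and any missing baseline values need simple imputation.
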